### Data Analysis

Collected data were entered into SPSS software (version 27.0; IBM Corp) before proceeding with data cleaning procedures. Both statistical and graphical normality tests were applied to continuous variables, such as age, knowledge, attitude, and self-efficacy. At baseline, the comparison of variables between groups used appropriate statistical measures based on the distribution of data. For normally distributed data, results are reported as mean (SD), and comparisons were conducted using an independent *t* test. For non-normally distributed data, results were reported as median (IQR), and comparisons were conducted using the chi-square test and the Mann-Whitney *U* test.

To evaluate the main effect of the IMB-based intervention modules on the response variables over time, as well as the group-time interactions, repeated-measures ANOVA was used for normally distributed data. For non-normally distributed data, generalized linear mixed models were applied to account for individual-level variability among participants, or generalized estimating equations were used when focusing on overall population-level trends. Intention-to-treat analyses were conducted separately for the intervention and control groups, and missing data were addressed using multiple imputations. Results were reported as differences between groups with 95% CIs. Statistical significance in this study was set at α=.05.

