## Abstract

**Background:**

Tuberculosis (TB) in children is one of the most significant public health crises in Somalia. This issue is aggravated by the fact that only 36.7% of children aged 12 to 23 months receive the Bacillus Calmette–Guérin (BCG) vaccine in Somalia, which helps prevent TB-disseminated diseases. Among the major factors that contribute to poor BCG uptake and TB prevention practices are the lack of maternal knowledge, negative attitude, and poor self-efficacy toward the BCG vaccine and TB prevention practices. As such, pregnant women play a vital role in ensuring timely, routine BCG vaccination for their newborns and adherence to TB prevention practices.

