### Study Population and Study Setting

The study population consists of pregnant women attending the Banadir Maternal and Child Hospital, Mogadishu, for ANC visits. The inclusion criteria include mothers with a gestational age range of 25 to 33 weeks, plans for postnatal follow-up at the hospital, and residence in Mogadishu, including internally displaced persons. The exclusion criteria include mothers who visited the hospital for other health conditions, those of non-Somali nationality, and those who had previous health education training related to immunization and TB prevention practices.

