### Outcome Assessment

Table 2 presents the primary and secondary outcome assessments, including the timing of each measurement.

**Table 2. T2:** Outcome measurements.

Outcome measure	Definition	Time of measurement		
		T0 (baseline)	T1 (2-month follow-up)	T2 (4-month follow-up)
Primary outcomes				
BCG^a^ uptake	Refers to receiving 1 dose of the BCG vaccine at birth. Infants who receive the vaccine after 6 weeks will be considered delayed.	No	Yes	Yes
TB^b^ preventive practices	Refers to the change in total practice scores of actions taken by participants to reduce the risk of TB infection and transmission, including respiratory hygiene (cough etiquette) and environmental control, between baseline, 2-month follow-up, and 4-month follow-up.	Yes	Yes	Yes
Secondary outcomes				
Knowledge	Refers to the total score change of participants’ knowledge regarding BCG vaccine benefit, schedule, and side effect, as well as knowledge of preventive practices (respiratory hygiene/cough etiquette and environmental control) between baseline, 2-month follow-up, and 4-month follow-up.	Yes	Yes	Yes
Attitude	Refers to the change in total attitude scores toward the BCG vaccine and preventive practices between baseline, 2-month follow-up, and 4-month follow-up.	Yes	Yes	Yes
Self-efficacy	Refers to the change in total scores reflecting participants’ confidence in their ability to obtain and receive the BCG vaccine, as well as their confidence in engaging in TB prevention practices between baseline, 2-month follow-up, and 4-month follow-up.	Yes	Yes	Yes

a BCG: Bacillus Calmette–Guérin.

b TB: tuberculosis.

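### The described analysis of BCG uptake, a primary outcome with no baseline value, names no baseline covariate; adjusting for the pre-allocation scores could add precision at almost no cost

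*Protocol article*

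**What the plan says.** All statements are in the protocol article.

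- **Effect models (Data Analysis).** One paragraph covers every response variable. Its purpose is "To evaluate the main effect of the IMB-based intervention modules on the response variables over time, as well as the group-time interactions". Normally distributed outcomes go to repeated-measures ANOVA. For the rest, "For non-normally distributed data, generalized linear mixed models were applied to account for individual-level variability among participants", with generalised estimating equations (GEE) as the alternative. No covariate is listed and none is excluded. BCG uptake is not discussed separately.
- **Baseline data (Data Analysis).** "At baseline, the comparison of variables between groups used appropriate statistical measures based on the distribution of data"; the tests named are the t test, chi-square and Mann-Whitney U.
- **BCG uptake (Outcome Assessment, Table 2).** A primary outcome, defined as "Refers to receiving 1 dose of the BCG vaccine at birth". It is marked as not measured at T0 and measured at T1 and T2. The practice, knowledge, attitude and self-efficacy scores are measured at all three times.
- **Timing (Data Collection).** Baseline data are collected before random assignment.
- **Rationale (Abstract, Background).** "Among the major factors that contribute to poor BCG uptake and TB prevention practices are the lack of maternal knowledge, negative attitude, and poor self-efficacy".
- **Entry (Study Population and Study Setting).** The trial enrols "mothers with a gestational age range of 25 to 33 weeks".
- **Allocation (Randomization, Allocation Concealment, and Blinding).** 1:1, individual, computer-generated; no stratification is mentioned.

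**The concern.** The four score outcomes have a T0 value, which enters their analysis as the first time point. BCG uptake has none. A model with group, time and their interaction therefore contains nothing measured before allocation for this primary outcome, unless a covariate is added.

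The trial holds good candidates. By its own account three T0 scores bear on uptake, and because they precede allocation they are legitimate covariates. Gestational age at entry is a fourth, since it relates to whether a woman has delivered by a given visit.

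The baseline tests do not fill the gap. Under proper randomisation they test a null hypothesis known to be true, and they do nothing to correct a chance imbalance in a prognostic variable. At stake is the width of the confidence interval for BCG uptake. The Sample Size section is built on the practice score alone, so the article contains no calculation showing that BCG uptake is adequately powered.

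**Working it through.** **No figure to reproduce.** The article gives no power or precision for BCG uptake and no association between any baseline variable and uptake. The size must therefore be shown as a range under assumptions.

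**Inputs**
- Control uptake 36.7%: the national coverage figure in the Introduction, *assumed* here to be the control rate.
- Intervention uptake 51.7%: *illustrative*, a rise of 15 points.
- Evaluable women: 185 per arm enrolled; with the planned 30% attrition, 185 × 0.70 = 129.5, taken as 129.
- Two-sided α = .05 (the article gives .05; two-sided is assumed).

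**Step 1. Unadjusted power.** Normal approximation, unpooled variance:

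SE = √{[p₁(1−p₁) + p₂(1−p₂)]/n}; power = Φ(0.15/SE − 1.96).

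The variance sum is 0.367 × 0.633 + 0.517 × 0.483 = 0.2323 + 0.2497 = 0.4820.
- n = 129: SE = √(0.4820/129) = 0.0611; 0.15/0.0611 = 2.454; power = Φ(0.494) = 69%.
- n = 185: SE = √(0.4820/185) = 0.0510; 0.15/0.0510 = 2.939; power = Φ(0.979) = 84%.

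**Step 2. How far adjustment could reduce the variance.** Simulation with 129 per arm and 4,000 runs per setting; control uptake 36.7% and intervention uptake 54.0% (the rate giving 80% unadjusted power). The unadjusted risk difference was compared with a logistic model standardised over one baseline score:

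| Assumed odds ratio per SD | Within-arm R² | Variance ratio, adjusted/unadjusted |
|---|---|---|
| 1.0 | 0.00 | 1.00 |
| 1.25 | 0.01 | 0.99 |
| 1.5 | 0.04 | 0.96 |
| 2.0 | 0.09 | 0.92 |
| 3.0 | 0.19 | 0.81 |

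The reduction runs from nil to about 19%. It stays at or below about 8% up to an odds ratio of 2.

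A separate simulation (150 per arm, 1,500 runs, one baseline predictor) gave ratios of 0.94, 0.88 and 0.84 at R² of 0.056, 0.109 and 0.190, with the same mean risk difference. With four independent covariates in place of one (129 per arm, 4,000 runs), the ratios were 1.01, 0.96, 0.92 and 0.82 at total R² of 0, 0.05, 0.11 and 0.19. Estimating more coefficients costs a little, and there is a very slight loss if none is prognostic.

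**Step 3. What this buys.** Multiply the variance by the ratio r; the equivalent extra women per arm are n/r − n:

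| r | Power, n = 129 | Extra per arm, n = 129 | Power, n = 185 |
|---|---|---|---|
| 1.00 | 69% | 0 | 84% |
| 0.94 | 72% | 8 | 86% |
| 0.88 | 74% | 18 | 88% |
| 0.84 | 76% | 25 | 89% |

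Worked line: r = 0.84, n = 129: SE = 0.0611 × √0.84 = 0.0560; 0.15/0.0560 = 2.677; Φ(0.717) = 76%; 129/0.84 − 129 = 24.6.

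**Step 4. Why gestational age belongs on the list.** Recruitment ran from 25 November to 21 December 2021 and sessions ended on 4 February 2022 (Results). Taking delivery at 40 weeks as an assumption, a woman at 33 weeks on 25 November is due 7 weeks later, on 13 January, before sessions ended. A woman at 25 weeks on 21 December is due 15 weeks later, on 5 April, about two months after the last session. Entry gestational age is therefore plausibly related to recorded uptake at T1.

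**The case against.** The strongest reply is that much of this rests on silence. The article condenses a fuller protocol, its analysis paragraph neither lists nor excludes covariates, and mixed models and GEE can carry them. **That stands.** A reader might infer that the BCG analysis uses no baseline information at all. The documents do not support this: they show only that no covariate is named. Multiple imputation is also planned with its variables unlisted, and T0 scores could enter there.

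A reader might also infer that baseline data are spent on significance tests instead of on estimation. That is too strong, because T0 values are part of the repeated-measures analysis of the four score outcomes.

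Nor is an unadjusted comparison wrong. In an individually randomised 1:1 trial it is valid and unbiased, its type I error already allows for chance imbalance, and unstratified allocation is no defect. **That stands too**, and it confines the point to efficiency.

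Gestational age at entry does not fix the infant's age at each visit. Visits are timed from the intervention, the interval from entry to session varies between women, and so do delivery dates. It is a plausible predictor and no more. Nothing in the article says that baseline tests will be used to select covariates.

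Finally, the gain may be small. The abstract calls the three constructs major factors but gives no strength of association, and the top of the range needs an odds ratio near 3 per SD.

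What survives is that, as described, BCG uptake is the one outcome with no route for baseline into its model, that suitable covariates are already collected, and that the baseline tests are stated in the text and are uninformative about the effect.

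**Conclusion.** The point holds as one of efficiency. As described, the primary BCG uptake analysis draws nothing from baseline, although three pre-allocation scores that the article itself links to uptake are available. Validity is not in question, and the documents do not establish that precision has actually been lost.

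The gain ranges from nil to about 19% of the variance of the risk difference, for assumed odds ratios of 1 to 3 per SD. In the illustration at 129 per arm, power goes from 69% to between 72% and 76% for variance ratios of 0.94 to 0.84. These figures rest on 36.7% as the control rate, an illustrative 15-point rise, the planned 30% attrition, and a prognostic strength that the documents do not give.

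**What to change.** Add to the Data Analysis section that:

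1. The BCG uptake model adjusts for T0 knowledge, attitude and self-efficacy scores and gestational age at entry, named in advance.
2. The result is a covariate-standardised risk difference with 95% CI, which matches the section's stated reporting of between-group differences.
3. Baseline variables are presented by arm without significance tests, and such tests are not used to choose covariates.

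Data collection ended in June 2022. If outcome data have already been analysed, label the adjusted result as a sensitivity analysis. The Ethical Considerations section already provides for notifying the registry and the university ethics committee of significant changes to analysis methods.

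The cost is a few sentences, a little more analysis work, no new data, and a very slight loss of precision if the covariates turn out not to be prognostic.

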### Data Collection

Data were collected using paper questionnaires at 3 distinct time intervals: baseline, 2-months postintervention, and 4-months postintervention. Participants were asked to complete a consent form before participating and were informed that their information would remain confidential and used solely for research purposes. The recorded data were securely stored in protected files, and individual responses were not reported publicly; instead, findings were presented in aggregate form. The random assignment took place on the same day that participants were selected for the study, after the collection of baseline data. To facilitate the data collection process, each participant was given a study follow-up card and was requested to carry them during each follow-up visit to the hospital.

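### The repeated-measures ANOVA names both a group main effect and a group-time interaction without saying which decides efficacy; with baseline as a level, the main effect estimates only two-thirds of the follow-up effect

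*Protocol article*

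**What the plan says.** The Data Analysis section of the protocol article sets one aim for the longitudinal analysis: "To evaluate the main effect of the IMB-based intervention modules on the response variables over time, as well as the group-time interactions". For that aim, "repeated-measures ANOVA was used for normally distributed data". Non-normal data go to another class of model: "For non-normally distributed data, generalized linear mixed models were applied to account for individual-level variability among participants", or generalized estimating equations. Effects are to be presented as follows: "Results were reported as differences between groups with 95% CIs". No visit or contrast is attached to that difference, and no baseline covariate is named.

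The Data Collection section gives the measurement times: "Data were collected using paper questionnaires at 3 distinct time intervals: baseline, 2-months postintervention, and 4-months postintervention". It also places random assignment after the baseline data were collected. Table 2 (Outcome Assessment) marks practices, knowledge, attitude and self-efficacy as measured at T0, T1 and T2, and defines each as a change. For the primary score the definition begins: "Refers to the change in total practice scores of actions taken by participants to reduce the risk of TB infection and transmission". BCG uptake, the other primary outcome, is marked as not measured at T0.

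**The concern.** In a repeated-measures ANOVA the group main effect is the difference between arms averaged over every level of the time factor. If T0 is one of those levels, a time at which no one has been treated counts for a third of the answer. Under randomisation the expected difference there is zero, so the average is pulled toward zero by a known factor. Any chance imbalance at T0 also enters the main effect unadjusted.

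The interaction asks a different question, namely whether the arms differ in their course over time. It matches the change-based definitions in Table 2. With three times, however, it is a 2-df test and gives no single difference with a confidence interval. The one overall between-group difference that this ANOVA yields directly is the diluted one.

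Two things are at stake for a primary outcome. The reported effect may be understated by a third. And with two named tests and no decisive one, the efficacy claim could rest on whichever is significant.

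**Working it through.** **Inputs from the documents.** Sample Size: means 20.71 and 18.45, SD 4.40, attrition 30%. Results: 185 per arm (abstract). Data Analysis: α = .05, taken as two-sided. Planned difference: 20.71 − 18.45 = 2.26. Evaluable per arm: 185 × 0.70 = 129.5, taken as 129.

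**Assumptions, because the documents give no figure.** Equal SD at each visit, the same correlation ρ between any two visits (compound symmetry), and ρ = 0.5 with a range of 0.3 to 0.7. T0 is taken as a level of the repeated factor, and the effect d as equal at T1 and T2.

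**The plan's own figure.** The article gives no effect estimate or power for the repeated-measures analysis. Its sample size inputs give 2 × (4.40 × 2.802 / 2.26)² = 59.5, so 60 per arm. Dividing by 0.90 × 0.70 gives 96 per arm, 192 in total, not 370. That is a separate matter. Here it means only that the larger enrolment cushions any loss of power.

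**Step 1: what each term estimates.**
- Group main effect: (0 + d1 + d2)/3, which is two-thirds of the mean follow-up effect (d1 + d2)/2 whatever d1 and d2 are. For 2.26 at both visits: (0 + 2.26 + 2.26)/3 = 1.51.
- Change contrast within the group-time interaction (mean of T1 and T2, minus T0): 2.26.
- Baseline-adjusted mean of T1 and T2: 2.26.

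A simulation of 4,000 trials (130 per arm, ρ = 0.5) gave 1.51 for the main effect and 2.26 for the change contrast.

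**Step 2: variance per woman, as a multiple of SD².**
- Main effect: (1 + 2ρ)/3 = 0.667 at ρ = 0.5
- Change contrast: 1.5(1 − ρ) = 0.75
- Baseline-adjusted mean of T1 and T2: (1 + ρ)/2 − ρ² = 0.50
- Baseline-adjusted single visit: 1 − ρ² = 0.75

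The standard error of the arm difference is 4.40 × √(2 × multiple / 129), which gives 0.447, 0.474, 0.387 and 0.474 in that order.

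**Step 3: power for an illustrative effect of 1.54 points.** This value is not in the documents. It is about what a simple two-sample comparison at one visit detects with 80% power: 2.802 × 4.40 × √(2/129) = 1.53. Power is Φ(effect/SE − 1.96). For example, the main effect is 1.54 × 2/3 = 1.027, and 1.027/0.447 = 2.30, giving 63%. For the 2-df interaction, the noncentrality is (129/2) × (2/3) × 1.54² / (4.40² × 0.5) = 10.5 on 2 and 512 df, giving 83%.

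| ρ (assumed) | Main effect | 2-df interaction | 1-df change contrast | Baseline-adjusted mean of T1 and T2 |
|---|---|---|---|---|
| 0.3 | 73% | 69% | 78% | 96% |
| 0.5 | 63% | 83% | 90% | 98% |
| 0.7 | 55% | 97% | 98.7% | 99.7% |

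A baseline-adjusted difference at one visit alone has about 90% power at ρ = 0.5, the same as the change contrast.

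**Step 4: power at the planned 2.26.** The main effect has 1.507/0.447 = 3.37, giving 92% at ρ = 0.5, 96% at ρ = 0.3 and 87% at ρ = 0.7. The 2-df interaction has 99% at ρ = 0.5.

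**Step 5: relative sample size at ρ = 0.5.** Against the baseline-adjusted mean, the main effect needs (0.667 ÷ 4/9)/0.50 = 3.0 times as many women, and the change contrast 0.75/0.50 = 1.5 times.

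**The case against.** A reader might infer that the planned ANOVA as a whole shrinks the treatment effect by a third and wastes the baseline score. The documents do not support that. The same sentence also names the group-time interaction: "as well as the group-time interactions, repeated-measures ANOVA was used for normally distributed data". That term is the usual test of intervention effect in a pre-post design, it is undiluted, and it fits the change definitions in Table 2. It uses each woman's baseline by subtraction, which also largely removes chance imbalance. This is less efficient than covariate adjustment but valid under randomisation. The dilution and the unadjusted imbalance belong to the main effect only.

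A reader might also infer that the trial lacks power. At the documented effect it does not: even the main effect stays above the planned 80% across ρ from 0.3 to 0.7. The larger gaps in power appear only at an illustrative effect and an assumed correlation.

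Nor does the article say outright that T0 is a level of the repeated factor, or that the main effect decides efficacy. It is a condensed article, and a fuller plan may specify the model. What remains is stated text, not missing detail: the article names as a target "To evaluate the main effect of the IMB-based intervention modules on the response variables over time", measures the scores at three times, defines them as change from baseline, and names no covariate. Reading T0 as a level is an inference, but a strong one.

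**Conclusion.** The point holds in a limited form and should be fixed. The plan names two terms and leaves open which one carries the efficacy conclusion. If T0 is in the model, one of them, the group main effect, estimates exactly two-thirds of the mean follow-up effect: 1.51 in place of 2.26 when the effect is equal at both visits. The factor of two-thirds needs only that T0 is a level and precedes randomisation. The power figures also need the assumed compound symmetry and ρ.

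At the planned effect the harm is mainly the understated estimate. For smaller effects the main-effect test also loses real power: at 1.54 points and ρ = 0.5, 63% against 83% for the interaction and 98% for the baseline-adjusted mean of the two follow-ups. The point covers the practices score and the three secondary scores where they are analysed by ANOVA. It does not touch BCG uptake.

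**What to change.** For practices, knowledge, attitude and self-efficacy:

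- Do not use the group main effect over T0 to T2 as an efficacy test or as the reported between-group difference.
- Fit a linear mixed model with the T1 and T2 scores as outcomes, and with arm, visit, arm-by-visit and the baseline score as terms.
- Report as the main contrast the baseline-adjusted difference between arms averaged over T1 and T2, with its 95% CI, and give the T1 and T2 differences alongside.
- If the sponsor prefers one visit as primary, name it. The documents do not favour T2 over T1, and a single visit should not be credited with the power of the averaged contrast (about 90% against 98% in the illustration above).

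The cost is wording and a re-specified model; no new data are needed. Follow-up data collection ended in June 2022, so record this as a change of analysis made before results are reported, and state whether any comparison between arms had already been seen. The Ethical Considerations section already commits to telling the registry and the university ethics committee of significant changes to analysis methods.

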### Ethical Considerations

The trial protocol was approved by the Ethics Committee for Research Involving Human Subjects at the Universiti Putra Malaysia (UPM) (UPM/TNCPI/RMC/JKEUPM/1.4.18.2), the Ethical Review Committee of the Ministry of Health of Somalia (MOHHS/DGO/1166/Feb2024), and Banadir Hospital (BH/30594/4/22). The study was registered on May 24, 2022, with the Pan African Clinical Trials Registry and assigned a unique identification number PACTR202105554130782.

A participant information sheet in the Somali language was provided in written form by trained enumerators to each participant, from whom informed consent was obtained. Participant information and identities remained confidential and used solely for the purpose of this research. Participation in the study was voluntary, and participants had the right to withdraw at any point during the intervention. Participants received compensation of USD 2.00 per follow-up visit to cover transportation costs.

Any significant protocol modifications, such as alterations to eligibility criteria, outcomes, or analysis methods, will be promptly communicated to both the Pan African Clinical Trials Registry and the Jawatankuasa Etika Universiti Putra Malaysia.

